### Process of evaluation

To determine the effects of the exercise program, an initial evaluation will be made before beginning the exercise program to assess the initial status of the participants (Pre). This evaluation will be compared with the evaluation made at the end of the intervention program (Post) at 12 weeks.

#### Primary outcomes

##### Cardiorespiratory and muscle fitness

A series of functional physical condition used in the scientific community especially in older persons will be used [29]. At present, this series of tests has reference values for different age ranges from 60 to 94 years and cut-off points for each test associated with physical independence [30].

Aerobic capacity: this will be measured with the 6-min walk test, measuring the maximum distance (meters) walked in 6 min by the participants [29].

In addition, to complete the evaluation of cardiorespiratory fitness of the older adults, an incremental protocol on a cycle ergometer will be carried out using a respiratory gas analyzer. Depending on the characteristics of the participants, adapted standard protocols will be used [31–34].

Lower limb strength: this will be evaluated with the sit and stand test for 30 s. The number of times in 30 s the participant can completely stand up from a seated position with the back straight and the feet on the floor without pushing with the arms will be counted. A test will be performed to become familiarized with the test [29].

In addition, a test will be carried out to evaluate the explosive strength of the lower limbs by performing 3 countermovement jumps with 30 s of rest between each jump on a force platform (Musclelab, Ergotest Technology AS, Langesund, Norway) [35].

Upper limb strength: This will be evaluated with the bicep curl test made with a 2 kg weight for women and a 4 kg weight for men. The number of elbow curls made in 30 s with each upper limb will be counted [29].

Hand grip strength: This will be evaluated with the hand grip strength test. This test will be done with a digital dynamometer [36]. The participants will remain in the standard bipedal position throughout the test with the arm in full extension. Each participant will perform the test twice (alternatively with the two hands) with a 1-min rest period between each measurement.

Motor Agility/Dynamic balance: This will be evaluated with the 8-foot up and go test. The patient must get up from a chair, walk 8 feet towards and around a cone and return to the chair in the shortest time possible [29]. The best of two attempts will be registered.

In addition, a static balance test will be carried out on a force platform (Musclelab, Ergotest Technology AS, Langesund, Norway). Three attempts will be made in standing position with eyes open and 3 attempts with the eyes closed (if possible) with 1 min of rest between each attempt.

Flexibility/extensibility of the lower limbs: This will be measured with the “sit and reach test”. The patient will be seated with the leg extended and will slowly reach forward along the extended leg in an attempt to touch (or pass) the toes [29]. The number of centimeters lacking to reach the toes (negative score) or the number of centimeters that the toes are passed (positive score) will be registered. The best value of two attempts will be registered.

Flexibility/extensibility of the upper limbs: This will be evaluated with the “back scratch test”. This test provides a general measurement of the range of shoulder movement. It measures the distance between (or superposition of) the middle fingers behind the back [29]. It will be measured with both hands twice.

##### Evaluation of the biomarkers

The extractions will be made one week before initiation of the program and one week after completing the intervention.

Oxidative stress and antioxidant enzymes: Determination of oxidized lipids by the thiobarbituric acid reactive substances (TBARS) (fluorimetry) technique. Determination of oxidized proteins by the Advanced Oxidation Protein Products (AOPP) (colorimetry) technique. Determination of antioxidants by the total thiols technique (colorimetry). Determination of nitrites and nitrates (colorimetry).

Antioxidant Enzymes: Superoxide dismutase (SOD), catalase (CAT), glutathion peroxidase (GPx).

Inflammatory markers: Interleukin 6 and 10 (IL-6 and IL-10). Adiponectin. Tumor necrosis factor (TNF)-alpha. Serum IL-6 and IL-10 inflammatory markers and TNF-alpha will be determined with Luminex-100 IS (Integrated system: Luminex Corporation, Austin, TX, USA) system using the multiplex Linco High Sensitivity Human Cytokine Panel Lincoplex assay kit (Linco Research, Inc., MO, USA). Adiponectin will be determined with the Luminex-100 IS (Integrated system: Luminex Corporation, Austin, TX, USA) using the multiplex Linco Human Gut Hormone panel assay kit (Linco Research, Inc., MO, USA).

#### Secondary outcomes

##### Pain

Pain will be quantified with a pressure algometer + pupilometer in older patients with post-COVID-19 sequelae.

Pupilometer: The pupillary dilatation reflex (PDR) mode allows monitoring the variation of the pupil in real time during the application of a stimulus and during a maximum of 60 s.

The FLASH mode of the pupilometer, pupillary luminic reflex (PLR) allows evaluation of the reflex of pupilar constriction by a flash of light of 320 lumens during 1 s.

The pain pupillary index (PPI) mode uses standardized electrical stimulation that increases by 10 in 10 mA (initiating the stimulus in 10 mA up to 60 mA).

Parameters of the pupilometer: basal and maximum diameter of the pupil, percentage of variation of pupil diameter (in %), variation of the pupil in mm and intensity of reflex of dilatation, latency.

The pain threshold, subjective response to different painful stimuli, and objective response obtained after tetanic stimulation of the median nerve will be measured.

Pressure algometer: This commercial apparatus allows the application of a controlled and quantifiable nociceptive stimulus on a body surface.

Algometers apply a pressure stimulus that can be useful for applying a standardized painful stimulus, having a different nature from that applied with the pupilometer which is a stimulus of electric origin.

##### Mental health

Psychosocial variables will be evaluated using the Hospital Anxiety and Depression Scale (HADS) [37], which is made up of 7 items for anxiety and depression. Each item of the anxiety subscale (HADS-A) and the depression subscale (HADS-D) will be scored on a scale of 4 points from 0 (none) to 3 (much more). The highest scores indicate the highest levels of anxiety or depression.

##### Sociodemographic characteristics and quality of life

With the use of questionnaires age, sex, gender, marital status, educational level, socioeconomic level, family history, perception of health, presence of other diseases, medication consumption and the use of health services will be registered following the questionnaires of the National Health Survey as well as quality of life measured with Short Form Health Survey 36—SF36 [38].

### Data collection, management and analysis

An instruction manual for data collection and patient follow-up along the intervention process will be created. This manual will include the methodology of data collection and a detailed description of all the instruments used to obtain the study data. An initial protocol will be used for data entry, which will include specifications aimed at minimizing coding errors. All the technical personnel involved will undergo training sessions on the field work to harmonize data collection. Standardized protocols for quality control and data filtration will be developed. A centralized database will be designed for the data of the different participating centers. A central analytical plan will be developed, and the group coordinator of the project (*Campus Docent Sant Joan de Déu*) will provide data analysis and reports of study data in an agreed format. Only the principal investigator and the expert in research methodology and statistics will have information on the trial data until the end of the trial. Only anonymized data of the participants will be recorded.

An expert in research methodology and statistics will be in charge of designing the methodological focus and the statistical techniques that will be used to analyze the data obtained of each variable. Briefly, descriptive statistics will be calculated for the overall sample and between the experimental groups taking into consideration the gender perspective. Subsequently, the corresponding parametric or non-parametric analyzes will be carried out to establish the minimum intra- and inter-group changes of the variables analyzed. Missing cases will continue in the final analysis, however, they will provide less information and decrease the variance of the estimated effects to a lesser extent than the existing cases at each assessment stage.

An α value ≤ 0.05 will be considered to indicate statistical significance. The final analysis of the study will be fully described and differences between the enrolled experimental groups will be presented to determine the effectiveness of the exercise programs.

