### Participants and criteria of eligibility

The sample will be made up of 120 eligible participants, over the age of 60 years who have had COVID-19 disease and present persistent COVID-19 symptomatology with sequelae of fatigue, muscle weakness, pain, difficulty in performing daily life activities, etc. diagnosed by the corresponding physician.

Participants will be recruited from internal medicine services and patients with post-COVID-19 sequelae will be selected from the database of the hospital and primary care centers who have given their consent to be contacted for participation in the research project. The recruitment status of the participants will be ongoing at the time of manuscript submission.

Candidates will fulfill the following inclusion criteria:Persons of both sexes (and different expression of gender) older than 60 years of age.Molecular diagnosis (reverse transcription polymerase chain reaction [RT-PCR]) of infection by SARS-CoV-2.No history of physical diseases and no disease or disability that limits participation in the exercise program or precludes the corresponding measurement/evaluations.Be able to communicate without difficulty.Be able to understand the objectives of the project and provide written, informed consent.Not taking any medication that can affect normal performance of the exercise program and the evaluations. Specifically, patients who were treated with IL-6 receptor antagonists (example: tocilizumab) during the last month will be excluded. This type of medications will interfere with the exercise adaptations of the cardiorespiratory system.

The following exclusion criteria will apply:Having acute or terminal disease or any other disease that may affect the normal practice of a supervised exercise program and the corresponding evaluations.Consumption of any amount of alcohol or drugs during the study.Be performing any type of activity that may interfere in carrying out the supervised exercise program or the evaluations.Not completing the study once initiated or wishing to participate in the control group.

To calculate the sample size of this project a type 1 (α) error of 5% and a 95% confidence interval with a level of precision (d = 0.095) was established for the test of proportional hypotheses resulting in a sample size of *n* = 108 persons, increased by 10% (rounded up to *n* = 120) to compensate for possible dropouts along the study period.

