To know the sample size more precisely in the hypothesis test of means it will be necessary to carry out a pilot study which will provide the size of effect and statistical power (0.80), determine the analysis to perform, obtain delta values in the units corresponding to the principal study variable as well as know the standard deviation. Since this cannot be carried out, the sample size described in the study by Udina and cols. (2021) [27] will be used, which established a slightly lower sample size (Total *n* = 33, subgroups of *n* = 20 and *n* = 13). Therefore, it is assumed that the theoretical sample calculation can be considered as correct given the above.

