#### Control group

The control group will not carry out any supervised exercise program but will maintain their same habits of daily life activities.

Each supervised exercise session will include 10 min of general warm up and mobility exercises. For quality adequate control of the program and to stimulate the practice of collective exercise, the sessions will be performed in groups of 10–15 participants. Different strategies will be used to improve program adherence and fulfillment. The participants of the intervention groups of the project will be informed of the importance of attending all the sessions of supervised exercise as well as the evaluations made before and after the intervention period. In addition, a series of motivation strategies will be established for the participants of the intervention groups to increase or maintain the index of adherence to the exercise program including group dynamics to improve cohesion among the participants.

The CG will be supervised by a weekly phone call made by the members of the research group will the aim of knowing their health status and inform them of the evaluation periods and any other aspect that the participants consider relevant.

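### The article gives two bases for judging efficacy, pre-to-post change and between-group difference, without saying which decides; only the between-arm contrast is randomised

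*Protocol article*

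**What the plan says.** Three statements in the protocol article bear on how an effect is judged.

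- **Process of evaluation.** To determine the effect of the programme, a Pre evaluation is made, and "This evaluation will be compared with the evaluation made at the end of the intervention program", at 12 weeks. The control group is not mentioned there.
- **Data collection, management and analysis.** After descriptive statistics, "the corresponding parametric or non-parametric analyzes will be carried out to establish the minimum intra- and inter-group changes of the variables analyzed". The threshold follows: "An α value ≤ 0.05 will be considered to indicate statistical significance". It is not limited to between-group tests.
- **Same section, last sentence.** Differences between the groups are to be presented in order to determine how effective the programmes are.

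The analysis section names no model and no covariate, and excludes none. It describes itself as brief and announces a central analytical plan.

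On delivery, the text under the Control group heading says of the supervised programmes that "the sessions will be performed in groups of 10–15 participants", and that group dynamics will be used to build cohesion. The control group receives a weekly phone call. The sample size paragraph makes no allowance for grouped delivery.

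**The concern.** The first statement makes pre-to-post change the measure of effect. The second puts intra-group and inter-group change side by side under one significance threshold. The third makes the between-group difference decisive. A reader of the final report could not tell from this text which result was meant to carry the efficacy claim.

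The distinction matters in this population. Participants are enrolled because they have persistent symptoms, so natural recovery and regression to the mean are plausible in every arm. Performance tests such as the 6-minute walk and the 30-second chair stand are repeated, so learning is plausible too. All of these would appear as within-arm improvement whether or not exercise works. Only the contrast between randomised arms removes them.

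Two further matters concern how well that contrast is estimated. A comparison of changes is less precise than a model that adjusts Post for Pre. And people who train together may have correlated outcomes, which would make naive standard errors too small in the exercise arms.

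**Working it through.** **The plan's own figure.** The sample size rests on "a type 1 (α) error of 5% and a 95% confidence interval with a level of precision (d = 0.095) was established". With one proportion and p = 0.5 (assumed; p is not given), n = 1.96² × 0.25 / 0.095² = 106.4, rounded up to 107, against the stated 108. That is close enough to count as reproduced. Dropout: 108 / 0.90 = 120, as stated. This calculation contains no between-group effect, pre-post correlation or design effect, so it neither supports nor refutes the point. It gives 30 per arm, or 108 / 4 = 27 after the planned dropout.

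**Inputs from the article:** 0.05 level (sidedness not stated; two-sided assumed); 27 to 30 per arm; training groups of 10-15, hence 30/15 = 2 to 30/10 = 3 groups per exercise arm. **Assumed, because the article gives no values:** common improvement, pre-post correlation r, intra-group correlation (ICC).

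**1. Within-arm tests when exercise does nothing.** Let every arm improve by 0.3 SD, with r = 0.7 and equal SDs at both visits.

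- SD of the change = √(2(1 − 0.7)) = 0.775
- Standardised change = 0.3 / 0.775 = 0.387
- Noncentrality with n = 27: 0.387 × √27 = 2.01; critical t on 26 df = 2.056
- Probability of a significant within-arm change = 0.491

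With n = 27, shifts of 0.2-0.4 SD and r of 0.5-0.8, the probability runs from 17% (0.2 SD, r = 0.5) to about 88% (0.4 SD, r = 0.8).

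**2. Baseline adjustment.** In units of the outcome variance, the change score has variance 2(1 − r) and ANCOVA has 1 − r². The ratio is (1 − r²) / (2(1 − r)) = (1 + r)/2.

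| r | Change score | ANCOVA | Ratio |
|---|---|---|---|
| 0.5 | 1.00 | 0.75 | 0.75 |
| 0.6 | 0.80 | 0.64 | 0.80 |
| 0.7 | 0.60 | 0.51 | 0.85 |
| 0.8 | 0.40 | 0.36 | 0.90 |

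For a 0.5 SD difference between two arms of 30 (assumed effect, normal approximation), power rises from 49% to 61% at r = 0.5 and from 86% to 90% at r = 0.8.

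**3. Training groups, if ignored.** The design effect in an exercise arm of groups of size m is DE = 1 + (m − 1) × ICC. The true standard error exceeds the naive one by √((DE + 1)/2) against the ungrouped control arm, and by √DE between two exercise arms. The actual two-sided error is 2(1 − Φ(1.96 / factor)).

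| ICC | m | DE | Factor, error vs control | Factor, error between exercise arms |
|---|---|---|---|---|
| 0.01 | 10 | 1.09 | 1.02, 5.5% | 1.04, 6.0% |
| 0.01 | 15 | 1.14 | 1.03, 5.8% | 1.07, 6.6% |
| 0.02 | 10 | 1.18 | 1.04, 6.0% | 1.09, 7.1% |
| 0.02 | 15 | 1.28 | 1.07, 6.6% | 1.13, 8.3% |
| 0.05 | 10 | 1.45 | 1.11, 7.7% | 1.20, 10.4% |
| 0.05 | 15 | 1.70 | 1.16, 9.2% | 1.30, 13.3% |

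At an ICC of 0.10 the error would be 10-13% against control and 16-21% between exercise arms.

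**The case against.** The strongest reply is that the article already judges efficacy between groups. The last sentence of the analysis section says so, and Study design sets the programmes against a control group. On that view the Process of evaluation paragraph only describes two visits, and intra-group changes may be reported alongside without harm. This has force, but it does not settle the matter: that paragraph opens with the purpose of determining the effect, and the 0.05 threshold covers intra-group tests with no rule of precedence.

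A reader might infer three stronger things, none of which the article supports.

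- **That the between-group tests are unadjusted and ignore baseline.** The article does not say this. It names no model, it defers detail to an analytical plan, and a comparison of changes already uses the baseline value. In a randomised trial such a comparison is unbiased, so preferring ANCOVA is a matter of efficiency.
- **That an arm will be declared effective because it is significant while the control group is not.** Under the assumptions in step 1, and with independent arms, that pattern would arise for at least one of the three exercise arms with probability 0.509 × (1 − 0.509³) = 0.44. But the article states no such rule, so 44% is not this trial's false-positive rate.
- **That standard errors will be too small.** This requires an ICC above zero and a final analysis that ignores it. The article gives the size of the training groups, not whether membership is fixed, and the analytical plan is not shown.

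**Conclusion.** The point holds in a limited form. The article offers two bases for efficacy without ranking them, and the pre-to-post one cannot separate exercise from changes common to all arms. With an assumed common improvement of 0.3 SD, r = 0.7 and 27 per arm, about half of such within-arm tests would be significant with no exercise effect.

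ANCOVA is an improvement on the stated comparison of changes, worth 10-25% of variance for r from 0.8 to 0.5. It does not correct a stated error.

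The training-group point is secondary and conditional. For an assumed ICC of 0.02-0.05, a nominal 5% test that ignored the groups would run at about 6-9% against control and 7-13% between exercise arms. The second range bears on the trial's aim of finding the most effective programme. At an ICC of 0.01 the inflation against control is under one percentage point.

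This should be addressed. Confidence is moderate, because the sizes rest on assumed values and the analytical plan is not available.

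**What to change.** - **Efficacy basis.** Reword Process of evaluation and the analysis section so that efficacy rests only on between-arm contrasts. Report within-arm changes descriptively, with intervals if wanted but without p-values.
- **Estimation.** State that each contrast comes from an ANCOVA of the Post value on arm and the Pre value of the same variable.
- **Training groups.** Record each participant's training group during delivery, including any moves between groups; if this is not captured then, it may not be recoverable later. Add a sensitivity analysis with a random effect for training group in the exercise arms only (a partially nested model), with small-sample degrees of freedom, and report the ICC.

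The cost is a few sentences and one recorded variable; no visit or measurement changes. The drawback is that with 2-3 groups per exercise arm the ICC will be poorly estimated and the clustered intervals will be wide. That is why the clustered model is proposed as a sensitivity analysis. If participants often switch groups, a model with one group per person will fit only approximately, and the analytical plan should say how such cases are handled.

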### Flexibility of the work plan

#### Limitations

The following limitations should be considered. The project will implement an intervention of 3 different programs of physical exercise in older patients with post-COVID-19 sequelae, and aims to determine which of the three programs is the most effective. The participants will be recruited through primary health care centers and hospitals, which makes the participant recruitment process difficult, and thus, the meetings of the supervisors of each center and with the medical personnel. The success of the process depends on medical recruitment, and it is difficult to assert that the complete estimated sample will carry out all the exercise programs. This is further complicated considering the possible study participant losses by persons who dropout for different types of reasons after having initiated the study (diseases, lack of motivation, post-COVD-19 symptomatology, among others).

On the other hand, during the intervention period, a series of strategies have been developed to promote adherence and participation with the aim of avoiding the greater than 10% dropout rate estimated for the study. Satisfactory adherence is considered with a minimum of ≥ 80% attendance to the scheduled exercise sessions. However, if the final expected sample size is not achieved in the initial recruitment or during the development of the exercise intervention programs and the dropout rate is higher than expected, a second recruitment and intervention phase could be implemented after the 5^th^ month of the project. If low recruitment continues and the estimated sample is lower than foreseen, the groups will be redistributed and patients with post-COVID-19 sequelae between 50–60 years of age will be included.

If with the previously described conditions we do not achieve a relevant sample based on the estimations made, a comparison will be performed between a group of older patients with post-COVID-19 sequelae who carry out a supervised plan with combined strength and aerobic exercises and a control group. In this case, it could not be investigated which exercise program is more effective, however, it could be determined if an exercise program combining aerobic stimuli of endurance with stimuli of strength is effective for improving persistent COVID-19 symptomatology is older people.

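### At least 21 measures are ranked equally as primary under one 0.05 threshold, and the aim of finding the most effective programme is tied to no variable or contrast

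*Protocol article*

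**What the plan says.** Protocol article, Primary outcomes, has two blocks.

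- **Cardiorespiratory and muscle fitness** begins with "Aerobic capacity: this will be measured with the 6-min walk test, measuring the maximum distance (meters) walked in 6 min by the participants". It continues with cycle ergometry with gas analysis, 30-second sit-to-stand, countermovement jump, biceps curl, hand grip, 8-foot up-and-go, static balance ("In addition, a static balance test will be carried out on a force platform"), sit-and-reach and back scratch.
- **Evaluation of the biomarkers** lists TBARS and AOPP, then "Determination of antioxidants by the total thiols technique (colorimetry). Determination of nitrites and nitrates (colorimetry"), then "Antioxidant Enzymes: Superoxide dismutase (SOD), catalase (CAT), glutathion peroxidase (GPx"), then "Inflammatory markers: Interleukin 6 and 10 (IL-6 and IL-10). Adiponectin. Tumor necrosis factor (TNF)-alpha".

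The Secondary outcomes heading comes only after these, with pain, mental health and quality of life.

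Data collection, management and analysis announces parametric or non-parametric analyses within and between groups and gives one threshold: "An α value ≤ 0.05 will be considered to indicate statistical significance". It mentions no allocation of that 5% across measures or arms. It also says that a central analytical plan will be developed.

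Study design sets out to find the most effective type of programme against control. Limitations repeats that the project "aims to determine which of the three programs is the most effective". Neither place attaches a variable, a contrast or a ranking rule.

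The sample-size text, describing what a pilot would supply, says it would "obtain delta values in the units corresponding to the principal study variable". No such variable is named anywhere.

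**The concern.** A trial with many equal primary measures and one nominal 5% threshold can succeed on any of them, so its overall chance of a false primary claim is well above 5%. Four arms add to this, because each measure allows three comparisons with control and six pairs.

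The ranking aim has a separate gap. The endurance and concurrent arms walk, and the 6-minute walk is a primary test. The strength and concurrent arms do circuit training, and several primary tests measure strength. Different arms could therefore lead on different primary measures, and the article has no rule to settle such a split. The choice of which result decides would then be open after the data are known.

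**Working it through.** **1. The plan's own figure.** The stated sample size is 108, raised to 120 (Participants and criteria of eligibility), from a 95% interval with precision 0.095 for a proportion. The proportion is not given; 0.5 is assumed here.

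n = 1.96² × 0.5 × 0.5 / 0.095² = 106.4, so 107, against 108 stated. Then 108 / 0.9 = 120.

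The figure reproduces to within one, but as the precision of a single proportion. None of the listed primary measures is described as a proportion, so the sample size does not reveal which one was meant to lead.

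**2. Count of primary measures.**

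- Fitness: 10.
- Oxidative stress: TBARS, AOPP, thiols, nitrites/nitrates counted once = 4.
- Enzymes: SOD, CAT, GPx = 3.
- Inflammation: IL-6, IL-10, adiponectin, TNF-alpha = 4.

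Total 10 + 4 + 3 + 4 = 21. This is a minimum: gas analysis, jumps, eyes open or closed, and two-sided tests can each give more than one variable.

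**3. Number of tests and expected false positives if no programme has any effect.**

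- One four-arm omnibus test per measure: 21 tests, 21 × 0.05 = 1.05.
- Three contrasts with control: 21 × 3 = 63 tests, 63 × 0.05 = 3.15.
- Six pairs: 21 × 6 = 126 tests, 126 × 0.05 = 6.3.

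**4. Chance of at least one false positive.** With independent tests:

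- 1 − 0.95^21 = 65.9%
- 1 − 0.95^63 = 96.1%
- 1 − 0.95^126 = 99.8%

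The last two ignore that contrasts share arms. A simulation allows for this: four arms of 30, 21 normal variables, equal correlation between variables, 4,000 runs per setting. The documents give no correlations, so all of them are assumed.

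| Correlation | Omnibus | 3 vs control, unadjusted | 6 pairs, unadjusted |
|---|---|---|---|
| 0 | 66% | 94% | 99% |
| 0.3 | 56% | 88% | 97% |
| 0.5 | 45% | 78% | 91% |
| 0.8 | 23% | 48% | 64% |

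The within-group analyses would add 21 × 4 = 84 tests, not counted here.

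**5. The same with one primary variable.** Simulated: about 5% with one omnibus test, 12% with three unadjusted contrasts with control, 20% with six unadjusted pairs.

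**6. Detectable difference at 80% power**, normal approximation, d = (z for two-sided alpha + 0.842) × √(2/n) in SD units.

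- 30 per arm, alpha 0.05: (1.960 + 0.842) × 0.258 = 0.72 SD.
- 30 per arm, 0.05/3 = 0.0167: (2.394 + 0.842) × 0.258 = 0.84 SD. At 27 per arm (30 less 10%): 0.88 SD.
- 30 per arm, 0.05/6 = 0.0083: 0.90 SD. At 27 per arm: 0.95 SD.
- 30 per arm, all 21 kept primary with 63 Bonferroni tests, 0.05/63 = 0.00079: 1.08 SD.

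**The case against.** The strongest reply is that the article is a condensed account. It introduces its methods as brief, assigns the techniques to an expert and announces a central analytical plan. A 0.05 threshold is compatible with adjusted p-values, or with an omnibus test followed by controlled comparisons. This stands: the absence of a named adjustment is not in itself the fault, and the number of contrasts is not fixed. A reader might infer that a false positive is almost certain. The documents do not support that, because it requires every contrast to be run unadjusted on weakly correlated measures with no true effect anywhere.

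A reader might also see a contradiction between the 21 primary measures and the singular principal variable in the sample-size text. That is weak evidence. The phrase lists what a pilot would provide, and the text then says the pilot cannot be done. It shows that no variable was named, not that one was chosen and then ignored.

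Two smaller points have some force. Cycle ergometry, the jump and static balance are introduced as additions and may be meant as complementary, although they stay under the primary heading. The six specific objectives also make a judgement domain by domain legitimate, but the article does not say that this is how programmes will be ranked.

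The reply does not reach the core. Which measure is primary, and what counts as the most effective programme, belong in the protocol. The article does not leave the primary outcomes open: it fixes them as 21 equals.

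**Conclusion.** The concern holds in a limited form. The article fixes at least 21 unranked primary measures, gives one 5% threshold for four arms with no error control stated, and promises a ranking of programmes without the variable or contrast that would decide it.

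If no programme works, the chance of at least one false primary finding is about 45-66% with one omnibus test per measure at correlations from 0.5 to 0. That is 9 to 13 times the nominal 5%. It is about 78-94% with three unadjusted contrasts against control, and about 91-99% with six unadjusted pairs. The range rests on assumed equal correlations, normal data and 30 per arm. Stronger correlation lowers it, to 23% for omnibus tests at 0.8, which is still well above 5%.

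Confidence is high that a primary variable and a ranking criterion are missing. It is lower on the exact size, because the testing scheme is not stated.

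**What to change.** Before outcome data are seen:

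1. The investigators name one primary variable from those already measured, or one per domain with alpha split across domains. It should preferably not be a task that only some arms train. The 6-minute walk, for example, would favour the walking arms.
2. Test the three exercise-versus-control contrasts on it with Dunnett or Holm control at 5%.
3. Compare the exercise arms with each other on the same variable with multiplicity-adjusted confidence intervals. Call a programme most effective only if its intervals against the other programmes exclude zero in its favour; otherwise report no ranking.
4. Reclassify the remaining measures as secondary or exploratory.

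This needs new wording and no new measurement. The cost is that fewer results will be called significant. At 30 per arm the difference detectable with 80% power rises from about 0.72 SD unadjusted to about 0.84 SD with three Bonferroni contrasts (about 0.88 SD at 27 per arm). With one variable for each of the two primary blocks, each contrast is tested at 0.05/2/3 = 0.0083, and the figure is about 0.90 SD (0.95 SD at 27). Keeping all 21 primary with 63 adjusted contrasts would need 1.08 SD, so naming one variable costs less. The protocol should state the detectable difference for the chosen variable, since the present sample size was not derived from any of the listed measures, and should acknowledge that at this size no programme may qualify as most effective.
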